### Questionnaire development and validation

2.2

The Parkinson’s disease risk survey questionnaire was developed and validated by an Expert Panel, consisting of movement disorder neurologists, Parkinson’s disease nurse specialists, and representatives from a PD support group (patients and caregivers). The questionnaire forms part of the Parkinson’s disease risk survey digital platform and participants complete it using a mobile smartphone device with responses input using the touch screen. Table 2 shows the content of the questionnaire translated into English. The original Thai version of the questionnaire can be found in Supplementary material 1. Details of questionnaire development and validation are described below.

**Table 2 tab2:** Parkinson’s disease screening questionnaire (English version).

	Yes	No
Have you ever noticed a tremor in your hands or legs at rest?		
Have you started writing slower or has your handwriting changed or become smaller?		
Have you noticed that you have become more clumsy or slower in any tasks: for example, combing hair, dressing, or bathing, or have more difficulty with tasks that involve fine hand motor control, such as doing up your buttons or opening a bottle?		
Have you noticed that your voice has become softer or more monotonous or that listeners have to ask repeatedly because they cannot hear you speak?		
Have you noticed that your arms swing less or do not swing when you walk?		
Do you walk with short steps or a shuffling gait?		
Do you have difficulty walking or freeze when starting to walk, while walking, or when turning?		
Do you have trouble with throwing yourself forward while walking causing you to keep up with your step or difficulty if you need to stop walking immediately?		
Do you have any of the following problems? Difficulty turning over when sleeping, getting out of bed or getting up after sitting down.		
Does your tremor, slowness, or stiffness start on one side of your body first?		
Do you know if you have symptoms of speaking, shouting or moving your arms and legs while dreaming or have you fallen off the bed while sleeping? Or have you ever been told by a bed partner or caregiver that you have these symptoms?		
Do you usually have excessive sleepiness during the day or fall asleep while doing an activity?		
Do you feel that your sense of smell has decreased?		
In the past 3 months, have you had chronic constipation, defined as defecating less than 3 times/week?		
Do you have symptoms of depression, for example, crying more easily than usual or a lack of interest in the surrounding environment or things that used to be fun in the past?		
Have you ever seen a hallucination or heard a sound without a person being present?		
Do you usually feel lightheaded or dizzy when changing position from supine or sitting to standing up, and do these symptoms usually improve or disappear after sitting or lying down?		
Do you usually have urinary control problems, such as being unable to control urine, urinary incontinence, or urinary retention?		
Do you have problems with analytical thinking, memory, or calculation that has worsened over more than 1 year?		
Do you have balance problems or frequent falls at the very beginning of experiencing tremor, slowness, or stiffness?		

#### Format

2.2.1

The Panel agreed that the survey should capture basic demographic data, information on the presence of, or exposure to, any potential risk factors or protective factors, and ask questions about motor and nonmotor PD symptoms, as well as potential atypical parkinsonian symptoms, that the individual might be experiencing. In terms of structure, focus and length, for the symptoms section of the survey, it was agreed that a total of 20 questions would be optimal to ensure participant engagement and completion of the survey. Questions are answered either “yes” or “no” and subjects’ responses are coded as “1” (yes) and “0” (no). Questions 1–10 relate to the presence of motor symptoms, questions 11–15 relate to the presence of nonmotor symptoms, and questions 16–20 determine the presence of “red flags” suggesting that the subject may have atypical parkinsonian disorders.

#### Feature selection

2.2.2

Screening questions for motor symptoms (questions 1–10) were developed based on the MDS clinical diagnosis criteria for PD (108) and questions on prodromal/nonmotor symptoms on the MDS Research Criteria for Prodromal Parkinson’s Disease (59). Symptoms and signs previously considered in PD and parkinsonism screening questionnaires from previous community and hospital-based PD screening questionnaire development studies were also comprehensively reviewed (109–112). The Panel then reached a consensus on those items that were likely to indicate the presence of prodromal PD most strongly (63, 64, 109, 111, 113, 114).

In terms of motor symptoms, tremor and shaking, bradykinesia and troublesome arm swinging, stiffness, gait and posture, and difficulty getting up after sitting down were good questions to discriminate between PD and healthy controls according based on sensitivity and specificity. The sensitivity and specificity, respectively, of tremor and shaking were: 85.8% (95% CI: 79.1–90.7) and 89.9% (95% CI: 82.3–94.6), bradykinesia and troublesome arm swinging: 72.7% (95% CI: 64.7–79.5) and 98.1% (95% CI: 92.6–99.7), stiffness: 88.9% (95% CI: 82.5–93.2) and 80.0% (95% CI: 71.1–86.8), gait: 69.0% (95% CI: 61.0–76.1) and 91.2% (95% CI: 84.6–96.0), posture: 59.4% (95% CI: 51.2 67.1) and 92.7% (95% CI: 85.7–6.6), difficulty getting up: 42.5% (95% CI: 34.6–50.7) and 82.7% (95% CI: 71.4–89.0). The combination of bradykinesia and slowness, gait and posture, and difficulty getting up was 87.5% and 86.3%, respectively. In a community survey, a problem was identified with question 9 relating to the phrase “difficulty getting up after sitting down” due to orthopedic problems in some respondents, so an additional question regarding “difficulty rising from bed or turning in bed” was added to question 9.

The five prodromal/nonmotor symptom questions (questions 11–15) were based on the published order of likelihood ratio (LR) (59, 65) and included hyposmia (LR 6.4), possible RBD based on questionnaire responses (LR 2.8), excessive daytime sleepiness (LR 2.7), constipation (LR 2.5), and depression (LR 1.6).

The five questions on “red flag” items relating to atypical parkinsonian disorders (questions 16–20) were derived from a review by the Expert Panel of the main symptoms that discriminate PD from the four main atypical parkinsonian disorders namely progressive supranuclear palsy, corticobasal syndrome, multiple system atrophy, and dementia with Lewy bodies, based published differential diagnostic criteria for these conditions (115–120) along with the red flags criteria of the MDS clinical diagnosis criteria for PD (108).

#### Validation

2.2.3

There are various different approaches that can be used for the assessment of content validity; however, a review of the published literature suggests that there is no agreed consensus on the best method for patient-focused instruments (121, 122). Some studies use Expert Panel opinion only without any grading while others propose 3-, 4-, or 5-item grading systems. In our study, the content validity of the symptom questionnaire was initially evaluated by the Expert Panel for both its relevance to the clinical presentation of prodromal and early PD, and its applicability to the Thai population. We also used a standard 3-level anchor system in rating the questionnaire, as used successfully in other PD questionnaire studies (114). Each item was graded in three levels (0 = not relevant, 0.5 = moderately relevant, 1 = very relevant) (114). The content validity was calculated as the mean score of all items with any mean score > 0.5 being considered acceptable. Using our chosen method, the content validity for the questionnaire was a mean ± standard deviation (SD) of 0.97 ± 0.07 (range: 0.85–1.0).

The reliability of the questionnaire was tested on a cohort of 15 people with PD (7 male, 8 female; mean [± SD] age: 67.6 ± 9.7) and 15 control subjects (7 male, 8 female; mean [± SD] age: 51.8 ± 9.0) without PD using Cronbach’s alpha coefficient of the total score. A Cronbach’s alpha coefficient > 0.7 was considered as indicating good reliability. The Cronbach’s alpha coefficient for the questionnaire was calculated to be 0.939. Test–retest reliability was evaluated in a cohort of 100 people with PD (54 male, 46 female) with 3 months between the first and second tests. Demographic characteristics of the test–retest study participants are summarized in Table 3. Significant test–retest reliability was confirmed for all 20 questions (*p* < 0.001 in each case). Pearson’s correlation between PD and the total sum score of the 20-item questionnaire was R = 0.931 (*p* < 0.001). The Pearson’s correlation for each individual item is shown in Supplementary material 2. The receiver operating characteristic (ROC) curve for PD classification using the symptoms questionnaire with 10-fold cross validation which showed a mean area under the curve (AUC) of 0.92 ± 0.02.

**Table 3 tab3:** Demographic characteristics of subjects who participated in the questionnaire test–retest validation.

Parameters	Male (*n* = 54)	Female (*n* = 46)	*p*-value (Chi-squared test)
Age, years (mean ± SD)	62.0 ± 14.8	56.1 ± 10.2	0.030^*^ (Unpaired *t*-test)
Status, %	Single 21.4%	Single 25.5%	0.933
	Married 66.7%	Married 61.8%	
	Divorced 4.8%	Divorced 3.6%	
	Unknown 7.1%	Unknown 9.1%	
History of drinking alcohol, %	No 47.6%	No 90.9%	<0.001^*^
	Yes 50.0%	Yes 9.1%	
	Quit 2.4%	Quit 0%	
History of drinking coffee, %	No 33.3%	No 40.0%	0.532
	Yes 67.7%	Yes 60.0%	
History of drinking milk, %	No 42.9%	No 30.9%	0.287
	Yes 57.1%	Yes 69.1%	
History of smoking, %	No 73.8%	No 96.4%	0.005^*^
	Yes 9.5%	Yes 1.8%	
	Quit 16.7%	Quit 1.8%	
History of consuming dairy products, %	No 66.7%	No 52.7%	0.213
	Yes 33.3%	Yes 47.3%	
History of undertaking physical exercise, %	No 38.1%	No 74.5%	<0.001^*^
	Yes 61.9%	Yes 25.5%	
History of pesticide exposure, %	No 97.6%	No 89.1%	0.135
	Yes 2.4%	Yes 10.9%	
Previous head injury, %	No 92.9%	No 98.2%	0.313
	Yes 7.1%	Yes 1.8%	
History of drug addiction, %	No 100%	No 100%	NA
Concomitant diseases, %	No 52.4%	No 43.6%	0.419
	Yes 47.6%	Yes 56.4%	
Diabetes mellitus	26.2%	23.6%	0.815
Hypertension	28.6%	23.6%	0.634
Dyslipidemia	4.8%	7.3%	0.695
Heart disease	4.8%	0%	0.185
Cerebrovascular disease	4.8%	1.8%	0.577
Gout	2.4%	0%	0.433
Benign prostatic hypertrophy	7.1%	0%	0.078
Knee osteoarthritis	0%	7.3%	0.131
Gastritis	2.4%	5.5%	0.631
Other	4.8%	18.2%	0.063

SD, standard deviation; ^*^statistically significant difference between groups at the *p* < 0.05 level.

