## Discussion

3

This article outlines the protocol for the Parkinson’s disease risk survey in Thailand which will implement screening of the national population for early signs of PD using a digital platform. Results of validation tests have demonstrated both the validity and reliability of the digital platform that comprises a symptom questionnaire and objective tests of a range of motor tasks, for population screening in both community and hospital settings, and its ability to discriminate between people with and without signs of PD. The first field study was undertaken in Nakhon Sawan Province in January 2024 and the survey is being rolled out throughout Thailand to all citizens over the age of 40 years. Data collection from individual citizens, from further provincial field tests, and from hospital screening stations is ongoing. Data collected from the survey will be used to identify subjects who have either prodromal PD or early signs of clinical PD.

Identification of strategies that could slow the human aging process, and thereby reduce the occurrence and impact of the many chronic noncommunicable diseases, such as PD, associated with advanced age, would undoubtedly have huge societal benefits, and have therefore been the focus of considerable research.

Lifestyle interventions that have been evaluated for their positive benefits in both health and disease prevention include exercise, dietary modifications and sleep. Looking at the available evidence for the benefits of these interventions, in healthy subjects, an 8-week treatment program that included diet, exercise and sleep guidance was shown to have a positive impact on parameters of aging (148). Analysis of patterns of DNA methylation, a recognized biochemical marker of age, in participants was used to calculate their DNAmAge. The program of lifestyle interventions was associated with a statistically significant 3.23-year decrease in subjects’ DNAmAge compared with controls, a potential reversal of epigenetic age.

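### Test–retest reliability of the 20 questionnaire items is declared from p < 0.001 in people with PD only, which does not establish agreement or support the reliability claim for population screening

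*Protocol article*

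**What the plan says.** Section 2.2.3 (Validation) reports two kinds of reliability evidence for the questionnaire.

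- **Internal consistency.** Cronbach's alpha was 0.939 in 15 people with PD and 15 controls. A magnitude threshold was set: "A Cronbach’s alpha coefficient > 0.7 was considered as indicating good reliability".
- **Test–retest.** This was "evaluated in a cohort of 100 people with PD", "with 3 months between the first and second tests". The result is one statement: "Significant test–retest reliability was confirmed for all 20 questions", with p < 0.001 in each case. The text names no test and gives no coefficient, confidence interval or acceptance threshold.

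Section 2.2.1 (Format) says that each item is answered yes or no and coded 1 or 0. Question 14 in Table 2 opens with "In the past 3 months, have you had chronic constipation".

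Section 2.1 sets the target population as all Thai citizens above 40 years. The Discussion (section 3) says that the validation results have "demonstrated both the validity and reliability of the digital platform", and applies this to population screening in community and hospital settings.

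**The concern.** Test–retest reliability is a matter of size: how often the same person gives the same answer twice, beyond chance. The p-value reported is most naturally read as a test of zero association between the two answers. With 100 people, a modest association is enough to reject that. Section 2.2.3 applies magnitude thresholds to content validity (above 0.5) and to Cronbach's alpha (above 0.7). Test–retest is the one property there that is declared from significance alone.

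The second gap is the population. All retested people had PD, while most people reached by a survey of citizens above 40 will not. Questions 10 and 20 ask how tremor, slowness or stiffness began, so they presuppose symptoms that many screened people will not have. Repeatability in diagnosed patients does not carry over by itself.

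What is at stake is a stated property of the instrument. The questionnaire is in all eight of the best ensembles in Table 7, so its repeatability matters to the platform. The documents give no basis for saying how far item noise would change who is referred.

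**Working it through.** **Inputs.** n = 100, people with PD only, 3-month interval, p < 0.001 for each item (section 2.2.3); binary items (section 2.2.1).

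**Reproducing the stated figure.** The p-values cannot be reproduced, because the text gives no coefficients, 2×2 counts or test name. The check is therefore run backwards: what is the smallest coefficient that gives p < 0.001?

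**Step 1. Pearson correlation (phi for 0/1 items), two-sided t-test.** With t(0.9995; 98 df) = 3.39:

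r = t / √(t² + n − 2) = 3.39 / √(11.49 + 98) = 0.324

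**Step 2. Chi-square, 1 df.** phi = √(10.83 / 100) = 0.329. A one-sided z-test gives 0.309.

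**Step 3. Translation to kappa.** Phi equals Cohen's kappa only when the yes-rate is the same at both tests. Whole-number 2×2 tables with n = 100 give these smallest values of kappa with p < 0.001:

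| Yes-rate, test / retest | Test used | Smallest passing kappa |
|---|---|---|
| Equal, 10–50% | Plain chi-square | 0.33–0.38 |
| Equal, 10–50% | Yates or Fisher | 0.36–0.44 |
| 50% / 30% | Plain chi-square | 0.32 |
| 60% / 30% or 70% / 40% | Plain chi-square | 0.30 |
| 80% / 50% | Plain chi-square | 0.28 |

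One example with 30% yes at both tests: 16 yes–yes, 14 yes–no, 14 no–yes, 56 no–no. Raw agreement is 72 / 100 = 0.72. Chance agreement is 0.3² + 0.7² = 0.58. Kappa = (0.72 − 0.58) / (1 − 0.58) = 0.333. Chi-square = 100 × 0.333² = 11.1, p = 0.0009. This item would count as confirmed, although 14 of the 30 who first answered yes answered no at retest. The table is hypothetical, not a description of any item.

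**Step 4. Precision at the boundary.** For a coefficient of 0.324, the Fisher z interval is tanh(0.336 ± 1.96 / √97), about 0.14 to 0.49.

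**Step 5. Sensitivity to n.** The percentages tested in Table 3 fit group sizes of 42 and 55 (total 97), not the 54 and 46 in its headers. At n = 97 the thresholds in Steps 1 and 2 become 0.329 and 0.334, so nothing here changes. The table headers should be reconciled separately.

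**Step 6. Population covered.** Test–retest: 100 with PD, none without. Cronbach's alpha: 15 with PD and 15 controls, but at a single sitting, so it says nothing about stability over time. The Discussion's claim covers general community and hospital screening. No retest in people without PD is described.

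**Step 7. Interval.** If test and retest are 3 months apart and question 14 asks about the past 3 months, the two answers refer to essentially separate periods. A changed answer may then be a true change. Among the 20 items in Table 2, only question 14 carries this window.

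**The case against.** Several points on the other side are sound.

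- **The floor is not an estimate.** An item whose true coefficient sits at 0.324 would pass only about half the time. If all 20 items sat there and were independent, the chance that all pass would be 0.5²⁰, about 1 in a million. For an even chance that all 20 pass, each must pass with probability 0.5^(1/20) = 0.966 (z = 1.825), which needs a common true coefficient of about tanh(0.336 + 1.825 / √97) = 0.48. Equal coefficients and independence are assumptions. Correlated items would soften this, and one item could still be weak. A reader might infer from the 0.32 that the items are in fact unreliable; the documents do not support that.
- **Supplementary material 2 is not shown.** It lists a Pearson correlation for each item. The text introduces these directly after the correlation between PD and the sum score, not as test–retest values, but the wording does not settle it. What can be said is that no test–retest coefficient is in the text shown.
- **The 3-month gap does not flatter the result.** True symptom change tends to lower agreement, so it makes p < 0.001 harder to reach. The interval clouds interpretation, mainly for question 14; it does not inflate reliability.
- **Reliability was also examined by Cronbach's alpha, with controls.** True, but internal consistency in 30 people does not replace a retest in people without PD.
- **Harm to screening is indirect.** The questionnaire is one classifier within a majority vote, and a neurologist confirms the diagnosis after referral. A reader might infer that unreliable items would push people across a referral line; the documents define no such line for the questionnaire and allow no such calculation.

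These points limit the size of the criticism. They do not turn a p-value into evidence of agreement, and they do not supply the missing population.

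**Conclusion.** The point holds in a limited form. The statement that test–retest reliability is confirmed for all 20 items rests, in the text shown, on significance against zero association. A coefficient of 0.324 (Pearson or phi) would meet that criterion at n = 100, and about 0.28 to 0.44 across the tests and yes-rates tried. Reliability is therefore unproven on this evidence, not shown to be poor, and the actual coefficients may be well above the floor.

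The extension to population screening is not supported by the test–retest data, because no retest in people without PD is described and Cronbach's alpha measures something else.

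This rests on three assumptions: that the unnamed test was one of zero association; that n was 100 (or 97, with no material difference); and that the item correlations in Supplementary material 2 are not the test–retest values, as their placement suggests. If they are, the missing magnitude may already exist for the items, but the mismatch between the retested and the screened population would remain.

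**What to change.** 1. From the paired answers already held, report raw agreement and Cohen's kappa with 95% CI for each item, and the ICC with 95% CI for the total score. State the yes-rate at each test, because kappa depends on it.
2. Base the reliability statement on these values, judged against a magnitude threshold that the authors state and justify, as they did for Cronbach's alpha. Name any item that falls short.
3. In section 2.2.3 and the Discussion, limit the test–retest claim to people with diagnosed PD over 3 months, and say that repeatability in people without PD has not been assessed.
4. Note that the retest of question 14 partly measures true change, because its recall window matches the interval.
5. Say explicitly what the item correlations in Supplementary material 2 are correlations of.

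The cost is a short re-analysis of existing data and changes of wording. The downside is that some items may prove only fair, and the reliability claim becomes narrower.

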##### Validation results

2.3.2.5

Table 6 summarizes PD classification performance using classifiers specialized for individual activity data, measured by the mean AUC with 10-fold cross validation. PD classification using balance data achieved the highest mean (±SD) AUC of 0.88 ± 0.06. The use of voice vowels resulted in a mean (±SD) AUC of 0.82 ± 0.04, which was the lowest value.

**Table 6 tab6:** Mean area under the receiver operating characteristic curve after 10-fold cross validation for each test activity.

Activity	Mean AUC ± SD
Balance	0.88 ± 0.06
Postural tremor	0.87 ± 0.06
Dual tapping	0.86 ± 0.05
Pinch-to-size	0.85 ± 0.05
Gait	0.84 ± 0.07
Questionnaire	0.83 ± 0.04
Voice sentences	0.83 ± 0.04
Rest tremor	0.83 ± 0.06
Voice vowel	0.82 ± 0.04

Test activities are sorted by their mean area under the curve (AUC) in descending order.SD, standard deviation.

Using voice vowel and voice sentence data ROC curves for PD classification using RF with 10-fold cross validation showed mean (±SD) AUC values of 0.82 ± 0.04 and 0.83 ± 0.04, respectively (Figure 6). Using resting tremor data and postural tremor data, ROC curves for PD classification using RF with 10-fold cross validation showed mean (±SD) AUC values of 0.83 ± 0.06 and 0.87 ± 0.06, respectively (Figure 7). Using dual tapping and pinch-to-size data, ROC curves for PD classification using RF with 10-fold cross validation showed mean (±SD) AUC values of 0.86 ± 0.05 and 0.85 ± 0.05, respectively (Figure 8). Using gait and balance data, ROC curves for PD classification using RF with 10-fold cross validation showed mean (±SD) AUC values of 0.84 ± 0.07 and 0.88 ± 0.06, respectively (Figure 9).

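### The questionnaire's validation figures are internally inconsistent: Table 3 fits 42 men and 55 women rather than 54 and 46, the AUC is 0.92 in one section and 0.83 in another, and R = 0.931 has no stated sample

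*Protocol article*

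**What the plan says.** All of the following is in the protocol article.

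- **Reliability cohort (Section 2.2.3).** Cronbach's alpha was "tested on a cohort of 15 people with PD (7 male, 8 female") and 15 controls.
- **Test-retest cohort (Section 2.2.3).** Test-retest reliability "was evaluated in a cohort of 100 people with PD (54 male, 46 female) with 3 months between the first and second tests". Table 3 describes this cohort under column sizes of 54 and 46. Its p-value column is headed as a chi-squared test, with an unpaired t-test noted for age.
- **Correlation (Section 2.2.3).** Directly after the test-retest result: "Pearson’s correlation between PD and the total sum score of the 20-item questionnaire was R = 0.931". No sample is named.
- **First AUC (Section 2.2.3).** The ROC analysis of the questionnaire used 10-fold cross-validation, "which showed a mean area under the curve (AUC) of 0.92 ± 0.02". No sample or algorithm is named.
- **Second AUC (Section 2.3.2.5, Table 6).** Under the title "Mean area under the receiver operating characteristic curve after 10-fold cross validation for each test activity", one row reads "Questionnaire 0.83 ± 0.04". The text after Figure 9 gives the range across the specialized classifiers as 0.82 to 0.88.
- **Digital-marker validation cohort (Section 2.3.2).** 343 people with PD and 230 controls.

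**The concern.** Three sets of figures that should describe one instrument do not fit together. The Table 3 percentages do not match its column sizes. The questionnaire has two cross-validated AUCs, 0.09 apart. The correlation with PD status follows a cohort in which PD status does not vary.

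The questionnaire is part of all eight best ensembles in Table 7. An AUC of 0.92 would put it above every digital marker in Table 6, where the best is balance at 0.88. An AUC of 0.83 ties it for sixth to eighth of nine. The Discussion and conclusion rely on this validation when they call the platform valid, reliable and accurate enough for national screening. A reader cannot tell which sample, or which figure, supports that.

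**Working it through.** **1. Table 3 denominators**

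Inputs: the 35 percentages in each sex column and the printed p-values. A percentage fits a column size n if some whole number k makes 100·k/n round to it.

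Examples:
- Single men, 21.4%: 11/54 = 20.4% and 12/54 = 22.2%, so no count out of 54 works; 9/42 = 21.4%.
- Single women, 25.5%: 11/46 = 23.9% and 12/46 = 26.1%, so no count out of 46 works; 14/55 = 25.5%.

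| Column | Stated n | Fit at stated n | Best n | Fit at best n |
|---|---|---|---|---|
| Men | 54 | 8 of 35 | 42 | 34 of 35 |
| Women | 46 | 7 of 35 | 55 | 35 of 35 |

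Between n = 20 and n = 120, only the doubles (84 and 110) fit equally well. The one misfit is male coffee drinkers, 67.7%. With 33.3% non-drinkers it sums to 101.0%; 28/42 = 66.7% would fit.

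The p-values settle the size:

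| Row | Printed | At 54/46 | At 42/55 |
|---|---|---|---|
| Age | 0.030 | 0.025 pooled, 0.021 Welch | 0.022 pooled, 0.030 Welch |
| Marital status | 0.933 | 0.940 chi-squared | 0.933 chi-squared |
| Smoking | 0.005 | 0.013 chi-squared | 0.005 chi-squared |
| Coffee | 0.532 | 0.676 Fisher, 0.547 chi-squared | 0.532 Fisher |
| Milk | 0.287 | 0.222 Fisher, 0.209 chi-squared | 0.287 Fisher |
| Knee osteoarthritis | 0.131 | 0.094 Fisher, 0.057 chi-squared | 0.131 Fisher |

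Age at 42/55, Welch: t = (62.0 − 56.1)/√(14.8²/42 + 10.2²/55) = 5.9/2.666 = 2.21, p = 0.030.

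Across the 16 two-by-two rows with a numeric p, Fisher's exact test at 42/55 returns the printed value to three decimals in 15. The exception is hypertension (0.643 computed, 0.634 printed). At 54/46 none of the 16 is reproduced by chi-squared, with or without continuity correction, or by Fisher.

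**2. The two AUCs**

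Gap: 0.92 − 0.83 = 0.09, which is 0.09/0.04 = 2.25 or 0.09/0.02 = 4.5 of the reported fold SDs. The stated range of 0.82 to 0.88 contains 0.83 and excludes 0.92.

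Which described cohort could give 0.92 ± 0.02?
- *The test-retest cohort*: everyone has PD, so an AUC is undefined.
- *15 + 15*: ten folds leave 3 people per test fold. With two of one class and one of the other there are 2 pairs, so the fold AUC moves in steps of 0.25 (ties count half). The tightest pattern near 0.92 is seven folds at 1 and three at 0.75: mean 0.925, SD = 0.25·√(0.7·0.3) = 0.115, against the reported 0.02.
- *343 + 230*: large enough, but this is the cohort of the section in which Table 6 reports 0.83.

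**3. R = 0.931**

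For a binary status with case share p, d = r/√((1 − r²)·p(1 − p)), and AUC = Φ(d/√2) if scores are normal with equal variance.
- p = 0.5: d = 0.931/(0.365 × 0.5) = 5.10; AUC = 0.9998.
- p = 343/573 = 0.599: d = 5.20; AUC = 0.9999.
- In reverse at p = 0.5: AUC 0.92 gives d = 1.99 and r = 0.70; AUC 0.83 gives d = 1.35 and r = 0.56.

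Without normality, a numerical search over arbitrary 0–20 score distributions with r held at 0.931 found lowest AUCs of 0.93 (p = 0.5), 0.92 (p = 0.599), 0.90 (p = 0.77) and 0.90 (p = 0.25), all with extreme shapes.

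**The case against.** **The AUCs and R could each be true.** The article never says that 0.92, 0.83 and 0.931 share a sample or a classifier. Table 4 gives no questionnaire count, so even the sample behind 0.83 is not explicit. This stands. A reader might infer that the figures are mutually impossible, but the documents show only that they are unreconciled and unattributed.

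**R need not imply near-perfect separation.** A sum of yes/no items may be skewed, with a floor among controls, and the search above reaches 0.92. R could also come from the 15 + 15 people. This too stands: an AUC near 1.00 follows only under equal-variance normal scores, and any conflict with the AUCs needs shared data.

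**Table 3 could reflect missing answers or swapped headings.** This fails. Missing answers cannot raise the female denominator from 46 to 55. With headings swapped, 3 of 35 male percentages fit n = 46 and 5 of 35 female percentages fit n = 54.

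**Table 3 drives no classifier result.** True. It compares demographics by sex in a reliability cohort, which limits the consequence.

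**Test-retest.** A reader might add that reliability rests on p < 0.001 alone. Per-item correlations are in Supplementary material 2, which is not shown and may cover this, so the documents do not establish it. Nor do they settle whether the sensors add anything over the questionnaire, since no questionnaire-alone accuracy is given beside Table 7.

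**Conclusion.** The point holds in three parts of different strength.

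- **Certain:** Table 3 describes 42 men and 55 women (97, of whom 42/97 = 43% are men), not 54 and 46 (100, 54% men). Most of its p-values are Fisher exact under a chi-squared heading, and the age test is Welch. The male coffee percentage and the hypertension p-value do not fit and look like misprints.
- **Unreconciled:** the questionnaire has two 10-fold cross-validated AUCs, 0.09 apart, and the higher one lies outside the article's own range for its specialized classifiers. No described cohort other than 343/230 plausibly gives 0.92 ± 0.02, so 0.92 is wrong, misattributed, or from a sample or model not described.
- **Conditional:** R = 0.931 is undefined in the all-PD cohort it follows. If it shared data with the AUCs, and those ranked people about as well as the total score does, it would be incompatible with 0.83, and 0.92 would need an extreme score distribution.

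This is a should-fix: the figures support the platform's validity claims and are cheap to correct, but no screening rule is shown to depend on Table 3.

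**What to change.** - **AUC.** Compute the questionnaire AUC once in the 343/230 cohort, with folds split by participant, and use that value in Sections 2.2.3 and 2.3.2.5. Alternatively, state the different sample and classifier behind 0.92 where it is reported.
- **R = 0.931.** Name the cohort, with its numbers of cases and controls, or withdraw the figure.
- **Table 3 and the Section 2.2.3 text.** Reconcile the cohort sizes with the data. Name the tests actually used (Fisher exact, chi-squared, Welch t). Check the male coffee percentage and the hypertension p-value.
- **Optional.** Give per-item kappa and a total-score ICC with 95% confidence intervals beside the test-retest p-values, since they measure agreement directly.

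The cost is a re-analysis of existing data and corrected tables. The headline questionnaire AUC may turn out less favourable than 0.92, though the documents do not settle that.
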